**Figure 1 figure1:**
[figure not shown]
Good School Toolkit programmatic theory of change.

The Good School Toolkit is one of the few school interventions with a demonstrated impact of reducing school violence in a resource-constrained setting, including teacher-to-student violence [25]. The Good Schools Study included a cluster randomized controlled trial [26,27], qualitative study [28], process evaluation [29], and economic evaluation [30]. During the trial, conducted in Luwero district in Uganda from 2012-2014, the toolkit was delivered to 21 intervention schools that were compared with 21 wait-list control schools. The trial found that the toolkit reduced the relative risk of past-week teacher-to-student physical violence by 42% [27]. Secondary trial analysis found that the toolkit reduced teacher-to-student past-week physical, emotional, or sexual violence (adjusted odds ratio [OR] 0.41, 95% CI 0.26-0.64) and any student-to-student past-week physical, emotional, and sexual violence (adjusted OR 0.70, 95% CI 0.51-0.96) [31,32]. Subsequently (from 2015), the toolkit was delivered to 19 of the wait-list control schools. While the intervention remained the same (see Table 1), during later delivery the intervention was implemented by *resource persons*, trained and supported by Raising Voices, rather than the Raising Voices program team.

**Table 1 table1:** The Good School Toolkit intervention delivered during the trial and later delivery to study schools.

TIDieR [33] guideline	Description of the toolkit
Brief name	Good School Toolkit
Why	The goal of the toolkit was to transform the operational culture at the school level such that violence against children is prevented. The toolkit draws on the Transtheoretical Model [34] and contains behavior change techniques that have been shown to be effective in a variety of fields [35] and have been included in interventions to change teacher behavior in primary schools [36,37] and reduce perpetration of intimate partner violence [38].

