### Power to Detect a Difference

We anticipate that our trial exposure group will be 50% (n=1201), and no exposure group 19% (n=456), of the total Wave 2 sample (assuming a conservative 70% follow-up, 2402/3431). We estimate 50% [2] of our no exposure group will report past-year experiences of physical, emotional, or sexual violence from a peer at Wave 2. In this case, the smallest difference we can detect between no exposure and trial exposure groups, assuming 70% follow-up, an α of .5 and power of .8, would be an 8% difference between groups (OR 0.73).

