### Regression Analysis Strategy

All analysis is exploratory and hypotheses generating rather than testing. To explore if the intervention influences later outcomes, we will compare across the trial and no exposure groups (1 vs 2.2) and original study arms (1 vs 2) first including all 42 schools and then repeated, dropping the 2 nonimplementation schools. To further explore differences between levels of exposure, we plan to compare between trial and the later delivery groups (1 vs 2.1) and across secondary exposure groupings (Figure 3). We will account for clustering by including original study primary school as a random effect in mixed-effect regression models [71]. Binary outcomes will be analyzed using mixed-effect logistic regression, with effect size presented as odds ratios. Continuous outcomes will be analyzed using mixed-effects linear regression, with effect size presented as mean difference. All unadjusted and adjusted analyses will include baseline school-level mean of outcomes, where available [72]. Adjusted models will additionally include covariates identified as potential confounders. All measures of effect will be presented with 95% confidence intervals and *P* values. Size and direction of effect will be considered along with *P* values when assessing the strength of associations [70]. Appropriate methods will be used to analyze numeric outcomes that are not normally distributed. For example, bias-corrected 95% confidence intervals will be estimated using nonparametric bootstrapping. The presence of effect modification will be assessed by comparing models fitted with and without an interaction term. Likelihood ratio tests with *P* values<.1, along with the direction and size of effect for each group, will be considered as evidence for or against modification. If there is evidence of modification, then stratum-specific effects will be calculated [73].

For self-reported exposure, propensity score–matching will be used to account for the likelihood that self-reported exposure is confounded by an individual’s propensity to report exposure. We will estimate what factors predict toolkit exposure using regression analysis [29], then calculate predicted probability of exposure and group adolescents with similar propensity scores. The analysis will compare outcomes across these propensity score exposure groups, including the score as a covariate in regression models [72].

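### The stated detectable difference (8 points, OR 0.73) treats adolescents as independent, although exposure is set by school and the analysis fits a school random effect

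*Protocol article*

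**What the plan says.** All of this is in the protocol article.

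- **Power to Detect a Difference.** The expected group sizes are given as "trial exposure group will be 50% (n=1201), and no exposure group 19% (n=456", after "assuming a conservative 70% follow-up, 2402/3431". For the comparator rate: "We estimate 50% [2] of our no exposure group will report past-year experiences of physical, emotional, or sexual violence from a peer at Wave 2". The error rates are "an α of .5 and power of .8". The conclusion is that the smallest detectable difference "would be an 8% difference between groups (OR 0.73". The section gives no ICC, design effect or number of schools.
- **Good School Toolkit Exposure Measures.** The trial group comes from 21 schools. The no exposure group comes from the 21 wait-list schools: Primary 7 students of 19 schools, and the students of the two schools that did not implement the toolkit.
- **Regression Analysis Strategy.** "We will account for clustering by including original study primary school as a random effect in mixed-effect regression models". Also: "All measures of effect will be presented with 95% confidence intervals".
- **Introduction, The Good School Toolkit Intervention.** The toolkit reduced "any student-to-student past-week physical, emotional, and sexual violence (adjusted OR 0.70, 95% CI 0.51-0.96" in the trial.

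**The concern.** Adolescents who attended the same primary school may have more similar outcomes than adolescents from different schools. When exposure also varies by school, the variance of the group comparison grows with cluster size and ICC. The planned regression allows for this, and so does the planned attrition comparison (Analysis Plan). The power section alone does not appear to. If so, the printed figure belongs to a different and more precise analysis than the one that will be run, and a reader would credit the primary comparison with more power than it has. The section lists its inputs and prints a finished result, so this is a figure that can be checked, not a detail left to another document.

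**Working it through.** **Inputs.** From the power section: n1 = 1201 (trial), n0 = 456 (no exposure), p0 = 0.50, power 0.80. Number of schools: 21 per side. Alpha and sidedness: the section prints .5 and gives no sidedness; two-sided 0.05 matches the planned 95% confidence intervals. ICC: not in the document, so a range is assumed.

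**Step 1: reproduce the stated figure.** With independent individuals, the detectable difference d solves

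d = (1.96 + 0.842) × √[p1(1 − p1)/1201 + 0.25/456], with p1 = 0.50 − d.

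This gives d = 0.0768, p1 = 0.423, OR = 0.734. A pooled-variance test gives 7.66 points (OR 0.734), and a continuity-corrected version 7.82 points (OR 0.730). All round to 8% and OR 0.73.

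The alternatives do not match:

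| Alpha | Detectable difference | OR |
|---|---|---|
| 0.05, one-sided | 6.8 points | 0.76 |
| 0.5, two-sided | 4.2 points | 0.85 |
| 0.5, one-sided | 2.3 points | 0.91 |

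So the figure is an individual-level calculation at two-sided 0.05, and the printed .5 appears to be a misprint.

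**Step 2: add clustering.** Mean cluster sizes are 1201/21 = 57.2 and 456/21 = 21.7. With design effect DE = 1 + (m − 1) × ICC in each group,

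d = 2.802 × √[p1(1 − p1) × DE1/1201 + 0.25 × DE0/456].

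Worked case, ICC 0.03: DE1 = 1 + 56.2 × 0.03 = 2.69 and DE0 = 1 + 20.7 × 0.03 = 1.62. The effective sizes are 1201/2.69 ≈ 447 and 456/1.62 ≈ 281. Solving gives d = 0.106. For a true 50% versus 42%, the standard error is 0.0379, so power = Φ(0.08/0.0379 − 1.96) ≈ 56%.

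| Assumed ICC | DE trial / no exposure | Detectable difference | OR | Power for 8 points |
|---|---|---|---|---|
| 0 | 1.00 / 1.00 | 7.7 points | 0.734 | 83% |
| 0.005 | 1.28 / 1.10 | 8.2 points | 0.72 | 78% |
| 0.01 | 1.56 / 1.21 | 8.8 points | 0.70 | 73% |
| 0.02 | 2.12 / 1.41 | 9.7 points | 0.675 | 63% |
| 0.03 | 2.69 / 1.62 | 10.6 points | 0.65 | 56% |
| 0.05 | 3.81 / 2.04 | 12.1 points | 0.61 | 45% |

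The detectable difference passes 8.0 points at an ICC of about 0.003. Pooled and unpooled variances agree to within 0.1 point and 1 percentage point of power.

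**Step 3: what the document hints about the ICC.** The trial interval 0.51 to 0.96 implies SE(log OR) = ln(0.96/0.51)/3.92 = 0.161. Taking the 3820 endline students as 1910 per arm, independence would give √[2/(1910 × p(1 − p))], that is 0.081 at p = 0.20 and 0.065 at p = 0.50. The squared ratios are about 4.0 and 6.2. With 3820/42 ≈ 91 students per school, the implied ICC is (4.0 − 1)/90 ≈ 0.03 to (6.2 − 1)/90 ≈ 0.06. The prevalence range is an assumption, and the OR is an adjusted one, so this is only an order of magnitude for that outcome at that time.

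**The case against.** **The shortfall depends on an ICC that the document does not give.** This stands. At ICC 0.003 or below the printed figure is essentially right, and the difference still rounds to 8 points up to about 0.0075. A reader might infer that the design certainly misses 80% power. The documents support that only on condition that the ICC is above about 0.003.

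**The trial's interval is a weak guide to the Wave 2 ICC.** This also stands. It concerns past-week violence between students who were in the same primary school. The Wave 2 outcome is past-year violence from students, coworkers or community peers, about four years later, mostly in other settings. Clustering by former primary school may be much weaker, so 0.03 to 0.06 should not be taken as the ICC for this study.

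**Precision may be recovered.** All models adjust for the baseline school mean of the outcome where available, and randomisation was stratified on baseline violence. Both could reduce between-school variance. Against this, the calculation assumes equal cluster sizes, while the no exposure group mixes one grade from 19 schools with all sampled grades from two. Unequal sizes would raise the design effect. The power section invokes none of these points.

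**Two further inferences are tempting and not supported.** One is that the study is underpowered even for a fully sustained trial effect. The trial's OR of 0.70 is for a different outcome and recall period, so it is no benchmark for that; even if it were used as one, power would be about 81% at ICC 0.01 and 72% at 0.02. The other is that the Discussion treats a nonsignificant result as proof of no impact. It speaks of what an absence of long-term impacts would suggest, and the regression strategy weighs size, direction, consistency and confidence intervals alongside P values.

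**Conclusion.** The point holds in conditional form. The stated 8 points and OR 0.73 come from a calculation without clustering at two-sided alpha 0.05, and do not correspond to the planned mixed model unless the ICC is about 0.003 or less. For ICCs of 0.01 to 0.05 the detectable difference is about 9 to 12 points (OR about 0.70 to 0.61), and power for 8 points is about 73% down to 45%. These values assume equal cluster sizes of 57 and 22, a 50% comparator rate, and no gain from baseline adjustment. The printed alpha of .5 is a separate error in the same sentence.

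Severity is moderate. A reader might take this as a defect that undermines the results, but the documents do not support that: the analysis is described as exploratory and hypothesis-generating, the sample can no longer change, and the school random effect accounts for clustering in the estimates and intervals. What is wrong is the power statement and the reassurance a reader would draw from it.

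**What to change.** Recalculate the detectable difference with a design effect. Take the ICC from the Wave 1 or trial endline peer-violence data, or show a stated ICC range, and note that clustering may differ for the Wave 2 outcome. Use the actual number of students per school in each exposure group and the achieved Wave 2 numbers in place of the assumed 70% follow-up. Correct alpha to .05 and state that it is two-sided. If credit is taken for adjustment on baseline school means, say how much and on what basis.

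The cost is one recalculation and a few reworded sentences. No new data are needed and the analysis model does not change. The stated figure will probably become less favourable. No new rule for interpreting null results is needed.

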### Data Management

All Wave 1 and Wave 2 survey data were captured, transmitted, and stored on a secure server using Open Data Kit. Raising Voices school-level implementation assessment data were initially captured on standardized Excel (Microsoft Inc) spreadsheets scorecard. All data will be transferred to Stata 15 (StataCorp LLP) for all data management processes and analysis. A data set containing Wave 1 data (2014) will be individually linked with Wave 2 data (2018-2019) and merged with school-level aggregate data from the Good Schools Study baseline survey (2012) and Raising Voices school-level program implementation assessment scorecard data (2017), to create one data set for analysis.

### Analysis Plan

Adolescents’ sociodemographic characteristics will be described for Wave 1 and Wave 2 and by intervention-exposure groupings. Descriptive statistics for continuous variables will include the number of observations, mean, and standard deviation (or median and interquartile range as appropriate). Categorical variables will be presented as numbers and percentages. We will formally test for differences in characteristics between those who participated in Wave 1 and 2 compared to Wave 1 only (eg, age, sex, number of meals eaten the day before, school grade, and original study arm). We will account for clustering by original primary school (by using the Stata *Svy* command) and Taylor linearized variance estimation to calculate standard errors, present corrected person chi-square for categorical data, and associated *P* values and 95% confidence intervals. Together, these will be considered as evidence toward differential attrition [70].

### Regression Analysis Strategy

All analysis is exploratory and hypotheses generating rather than testing. To explore if the intervention influences later outcomes, we will compare across the trial and no exposure groups (1 vs 2.2) and original study arms (1 vs 2) first including all 42 schools and then repeated, dropping the 2 nonimplementation schools. To further explore differences between levels of exposure, we plan to compare between trial and the later delivery groups (1 vs 2.1) and across secondary exposure groupings (Figure 3). We will account for clustering by including original study primary school as a random effect in mixed-effect regression models [71]. Binary outcomes will be analyzed using mixed-effect logistic regression, with effect size presented as odds ratios. Continuous outcomes will be analyzed using mixed-effects linear regression, with effect size presented as mean difference. All unadjusted and adjusted analyses will include baseline school-level mean of outcomes, where available [72]. Adjusted models will additionally include covariates identified as potential confounders. All measures of effect will be presented with 95% confidence intervals and *P* values. Size and direction of effect will be considered along with *P* values when assessing the strength of associations [70]. Appropriate methods will be used to analyze numeric outcomes that are not normally distributed. For example, bias-corrected 95% confidence intervals will be estimated using nonparametric bootstrapping. The presence of effect modification will be assessed by comparing models fitted with and without an interaction term. Likelihood ratio tests with *P* values<.1, along with the direction and size of effect for each group, will be considered as evidence for or against modification. If there is evidence of modification, then stratum-specific effects will be calculated [73].

For self-reported exposure, propensity score–matching will be used to account for the likelihood that self-reported exposure is confounded by an individual’s propensity to report exposure. We will estimate what factors predict toolkit exposure using regression analysis [29], then calculate predicted probability of exposure and group adolescents with similar propensity scores. The analysis will compare outcomes across these propensity score exposure groups, including the score as a covariate in regression models [72].

For the primary peer-violence victimization outcome, we will present unadjusted and adjusted mixed-effect logistic regression models exploring the association between intervention exposure measures and peer-violence victimization.

For the secondary outcomes, we will present unadjusted and adjusted mixed-effect logistic or linear regression models exploring the association between intervention exposure measures and secondary outcomes. The effect of intervention exposure on secondary outcome measures will be assessed by the size of effects and accompanying *P* value and 95% confidence intervals, as well as expected direction and consistency across results.

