**Methods:**

This is a nonrandomized quasi-experimental 4-year follow-up study of adolescents who attended the 42 Good Schools Study primary schools in 2014; 21 schools initiated the Good School Toolkit intervention during the trial from 2012, and 19 schools initiated the intervention after the trial (during the later delivery phase) from 2015; 2 schools did not implement the intervention. Students in the final school grade (Primary 7) during 2014 of the 19 primary schools in the later delivery phase are expected to have left school prior to toolkit delivery in 2015. Wave 1 data were collected in 2014 from 3431 grade Primary 5 to Primary 7 school students aged 11-14 years; these students were followed up in 2018-2019 when aged 16-19 years and invited to participate in the Wave 2 survey. Data were collected in face-to-face interviews by trained Ugandan field researchers. Toolkit exposure groups are defined as exposed during the Good Schools Study trial (from 2012), as exposed during later delivery (from 2015), or not exposed including those expected to have completed Primary 7 prior to later delivery or from the 2 schools that did not implement the toolkit. Associations between outcomes at Wave 2 and toolkit exposure groups will be analyzed using mixed-effect multivariable logistic and linear regression models for binary and continuous outcomes, respectively. This analysis is exploratory and aims to generate hypotheses on if, and under what circumstances, the toolkit influences later adolescent outcomes.

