### Good School Toolkit Exposure Measures

#### Primary

Participants in 21 trial intervention schools and those in the 21 wait-list control schools are categorized as the original study arms (1) trial and (2) wait-list control. Further subcategories defined within the wait-list control are adolescents who were attending Primary 5 or 6 in the 19 later delivery schools as the (2.1) later delivery exposure group; adolescents who attended one of the schools that did not implement the toolkit or who were attending Primary 7 in one of 19 later delivery schools at Wave 1 (as these students are expected to have left school prior to intervention delivery) as the (2.2) no exposure group (Figure 3).

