**Retention in school outcomes**				
		Staying in school	Last school grade completed will be assessed in relation to current age and grade at Wave 1, for example, binary outcomes: completion of grade Primary 7 (yes=1, no=0), transition to secondary school measured as completion of grade Secondary 1 (yes=1, no=0)	Not applicable

The primary outcome is peer violence victimization. A peer is defined as students, coworkers, or community members of a similar age. Adolescents’ self-reported experience of peer violence in the last year will be measured using an adapted subset of questions from the International Society for the Prevention of Child Abuse and Neglect Child Abuse Screening Tool—Child: Institutional [61]. Questions were previously piloted and used in the Wave 1 survey [32]. For this analysis, peer violence is defined as violence from students, coworkers, or community members of a similar age. Experience of past-year peer violence will be constructed as a composite binary measure, with positive responses to one or more question items on acts of physical, emotional, and sexual violence coded as 1, and no acts coded as 0.

Secondary violence outcomes will be constructed as single and composite binary measures—as described above—for the primary outcome. Secondary violence outcome measures include past-year self-reported use of peer violence, girls’ experience and boys’ use of intimate-partner violence, measured using question items from the WHO multicountry Study on Women’s Health and Domestic Violence [51] and Conflict in Adolescent Dating Relationships Inventory [52,53,62] adapted and used during Wave 1. Intimate partners include boy/girlfriends, husbands/wives, and casual dating partners. Self-reported intimate-partner violence will be explored as a combined measure and separately by violence type (emotional, physical, and sexual).

We will measure attitudes toward teacher violence with a 3-item measure developed for the Good Schools Study and used during the Wave 1 survey [41]. A shortened 18-item Gender Equitable Men scale, previously validated among Ugandan adolescents [54], will be used to measure gender-equitable attitudes. Question items and subsets of questions, including attitudes toward domestic violence, will be explored as single items and composite outcomes. Response options for all attitude questions are on a 4-point Likert-type scale.

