### Potential Confounders and Effect Modifiers

The following factors have been identified a priori as potential confounders or effect-modifiers to the exposure-outcome relationships of interest: biological sex and the number of meals eaten the previous day (as a proxy for socioeconomic status that is expected to be associated with staying in the study school throughout intervention delivery and associated with later violence outcomes). In addition, and as appropriate for specific exposure-outcome relationships, the following variables have been identified as potential effect-modifiers or confounders measured at Wave 1: school grade, family connectedness, and experiences of violence outside of school [68,69].

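### The trial versus no exposure and trial versus later delivery contrasts mix toolkit exposure with school grade, and no planned contrast guarantees a same-grade unexposed comparison

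*Protocol article*

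**What the plan says.** All references are to the protocol article.

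- **Cohort.** The abstract's Methods paragraph says "Wave 1 data were collected in 2014 from 3431 grade Primary 5 to Primary 7 school students aged 11-14 years".
- **Arms.** Under Good School Toolkit Exposure Measures, Primary, the article states: "Participants in 21 trial intervention schools and those in the 21 wait-list control schools are categorized as the original study arms". There is no grade restriction on the trial group.
- **Split of the wait-list arm.** The same section defines "adolescents who were attending Primary 5 or 6 in the 19 later delivery schools as the (2.1) later delivery exposure group". The no exposure group (2.2) is made up of those in the schools that did not implement the toolkit, and those "who were attending Primary 7 in one of 19 later delivery schools at Wave 1".
- **Contrasts.** The Regression Analysis Strategy says "we will compare across the trial and no exposure groups (1 vs 2.2) and original study arms (1 vs 2"), with a repeat that drops the two nonimplementing schools, and then adds 1 versus 2.1. Power to Detect a Difference is worked out for 1 versus 2.2.
- **Covariates.** Potential Confounders and Effect Modifiers names sex and meals eaten for general use. It then says "as appropriate for specific exposure-outcome relationships, the following variables have been identified as potential effect-modifiers or confounders measured at Wave 1: school grade", followed by two other variables. Age is not on the list.

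**The concern.** Within the wait-list arm, grade decides exposure. P7 pupils of the 19 schools are unexposed, and P5 and P6 pupils of the same schools are exposed from 2015. The trial group is not split in this way. Whichever part of the wait-list arm is set against the whole trial group, the two sides differ in grade, and so in age at Wave 2, as well as in exposure. If peer violence or another outcome varies with grade, part of that variation will be read as a toolkit effect, or will hide one.

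This affects the contrast that is listed first and that carries the power statement. The original-arm contrast (1 versus 2) is balanced on grade by design, but its comparator includes the later-exposed P5 and P6 pupils, so it does not answer the exposed versus unexposed question.

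**Working it through.** **Inputs.** From Power to Detect a Difference: trial group 1201, no exposure group 456, total 2402, 50% event rate in the comparator, power 0.8, stated detectable difference 8% (OR 0.73). From Sampling: 21 trial schools and 21 wait-list schools, of which 19 implemented later and 2 declined. The article gives no P7 count. I assume equal school sizes and the same P7 share in both arms, and then vary the first.

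**1. The plan's own figure.** For two proportions, normal approximation, two-sided alpha 0.05 and no clustering, the approximate detectable difference is

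d ≈ (1.960 + 0.842) × √(0.25/456 + 0.25/1201) = 0.077.

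The exact solution is 7.66 points, OR 0.734, which rounds to the stated 8% and 0.73. The article prints alpha as .5, which would give 4.2 points two-sided, so the stated result evidently used 0.05 with no design effect.

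**2. Grade mix of each group.**

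- Wait-list arm: 2402 − 1201 = 1201.
- Pupils in the two declining schools: 2/21 × 1201 ≈ 114.
- P7 pupils in the 19 schools: 456 − 114 ≈ 342.
- P7 share: 342 / (1201 − 114) ≈ 31%.
- P7 pupils in all 21 wait-list schools: 0.314 × 1201 ≈ 378.
- P7 share of group 2.2: 378/456 ≈ 83%.
- P5-P6 pupils in group 2.2: 456 − 378 ≈ 78, all from the two declining schools.
- Group 2.1: 1201 − 456 = 745, or 62% of the wait-list arm, none of them P7.

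**3. Mean Wave 1 grade, with P5 and P6 taken as equally frequent.**

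- Group 1: 0.314 × 7 + 0.686 × 5.5 ≈ 5.97.
- Group 2.2: 0.828 × 7 + 0.172 × 5.5 ≈ 6.74, a gap of 0.77.
- Group 2.1: 5.5, a gap of 0.47 in the opposite direction.

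**4. Sensitivity to school size.**

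| Share of wait-list sample in the two declining schools | P7 share of group 2.2 | P7 share of group 1 | Grade gap, 1 vs 2.2 |
|---|---|---|---|
| 2% | 97% | 37% | 0.90 |
| 2/21 (equal sizes) | 83% | 31% | 0.77 |
| 15% | 71% | 27% | 0.66 |

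**5. What a grade trend would do.** This is illustration only. With no toolkit effect and an assumed linear trend of 1, 3 or 5 points per grade, the spurious unadjusted 1 versus 2.2 difference is 0.77 × 1, 3 or 5 ≈ 0.8, 2.3 or 3.9 points. The last is half of the 7.7-point detectable difference (3.9/7.7 ≈ 0.5).

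**6. What grade adjustment can do.** With the two declining schools dropped, group 2.2 has no P5 or P6 pupils, so a model with categorical grade draws its 1 versus 2.2 estimate from P7 alone. With them kept, all of the roughly 78 P5-P6 comparators come from two schools that chose not to implement.

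**7. P7 by original arm.** P7 pupils of all 21 wait-list schools are expected to be unexposed: in 19 schools because they should have left before delivery, in two because there was none. With about 378 per arm the detectable difference is 10.1 points (OR 0.66), against 7.7 for 1 versus 2.2, both without clustering. Over the range in step 4 it is 9.4 to 10.9 points. With an assumed design effect of 1.5, the two figures are about 12.4 and 9.4 points.

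**The case against.** The other side has good points, and several stand.

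- **Grade is named in advance.** The strategy section says adjusted models include covariates identified as potential confounders, and an article may leave the per-model list to a fuller plan. That is fair, but the text makes grade conditional, and grade is what defines the comparison group here.
- **The P7 contrast is within reach of the planned methods.** Grade is a possible effect modifier, and stratum-specific effects follow if an interaction is found. The P7 stratum of 1 versus 2 is then the wanted contrast. A reader might infer that the plan rules it out. It does not, but it leaves it to an interaction result.
- **Retention is handled.** A reader who sees only "completion of grade Primary 7 (yes=1, no=0" might infer that trial P5 pupils are unfairly set against pupils who had already reached P7. The same table entry, and the text after it, assess retention in relation to Wave 1 grade and current age, so that reading is not supported.
- **Unadjusted models.** It is tempting to demand grade in these too. Leaving covariates out is what makes them unadjusted, and adjusted models are shown beside them.
- **The P7 contrast is not a clean randomised comparison.** Schools were randomised in 2012, but pupils were sampled in 2014 after 18 months of delivery, 10% did not agree to follow-up, and 70% Wave 2 follow-up is assumed. The article itself hypothesises that the toolkit reduces dropout, so who reached P7 may depend on arm. Same grade is also not same age.
- **The analysis is labelled exploratory,** and the Limitations admit that groups differ on factors other than exposure. This lowers the stakes, but the Limitations do not name grade or age.

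**Conclusion.** The point holds in a limited form. By the article's own definitions, 1 versus 2.2 sets P5-P7 against a group that is about four-fifths P7 (71% to 97% over the school sizes tried; entirely P7 when the two declining schools are dropped), and 1 versus 2.1 sets P5-P7 against P5-P6. Both mix exposure with grade and age, grade control is conditional, and no planned contrast is certain to give a same-grade unexposed comparison.

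The imbalance follows from the definitions. Its percentages rest on equal school sizes and an equal P7 share in both arms. The consequence cannot be sized: the article gives no trend by grade, so the points in step 5 show scale only and say nothing about direction. A reader might infer that nearly all of the no exposure group is P7; with all 42 schools in, that overstates it. Nor do the documents show that a P7-only analysis must replace 1 versus 2.2, since it gives up precision and answers a narrower question.

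**What to change.** 1. Add a pre-stated comparison of P7 pupils by original arm across all 42 schools, and report it beside 1 versus 2.2. Describe it as protected by school-level randomisation, with a comparator expected to be unexposed, and still subject to 2014 sampling, refusal of follow-up and Wave 2 loss.
2. Restrict 1 versus 2.1 to pupils in P5 or P6 at Wave 1.
3. Include Wave 1 grade as a categorical covariate in every adjusted 1 versus 2.2 model. State that, without the two declining schools, the estimate then comes from P7 pupils only.
4. Name grade and age in the Limitations as a built-in difference between the exposure groups.

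The cost is wording and some extra model runs on data already collected; the article's Results section says that analysis has not been conducted. The P7 contrast is less precise (step 7), which is why it should stand beside 1 versus 2.2 and not replace it.
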